## Statistical considerations

### Sample size calculations and assumptions

The primary efficacy aim of this study is to demonstrate the incidence rate of access site-related BARC type III or V bleeding is reduced compared with the historical incidence rate. The secondary efficacy aims are to estimate the incidence rate of activation of each of the EBBMS level 1, 2, and 3 indicators and the incidence rate of all BARC type III or V bleeding and to investigate whether there is an association between the level of indicator and BARC type. The safety aim is to estimate the overall complication/adverse event rate as well as the adverse event rates related to the EBBMS.

The PROTECT II study enrolled 216 patients undergoing nonemergent high-risk PCI under MCS with Impella support.^16^ Investigators reported a major bleeding rate (defined as BARC III or V bleeding) of 12.5%. In the SAFE-MCS study, a 50% reduction in access-site bleeding rate (P) under surveillance with the EBBMS is estimated. The magnitude of reduction was chosen based on what was perceived to be clinically meaningful by the medical trial leadership and took into account that not all bleeding events are access-related and could be reduced by the use of the Saranas EBBMS. Assuming that the rate of bleeding (P) is 6.25%, a sample size of 184 evaluable subjects is required to achieve 90% power for a 1-sample exact binomial test at the 1-sided 0.05 alpha level.

Data will be summarized by sample size (N), mean, standard deviation, minimum, median, and maximum for continuous variables and by sample size and frequency and percentage of discrete variables. For all subjects included in this study, demographics (age, sex, race/ethnicity), medical history, physical examination, and laboratory tests will be summarized.

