### Primary end points

The primary end point is incidence of access-site related bleeding (Bleeding Academic Research Consortium [BARC]^14^ type III or V). For the principal analysis of the primary end point, bleeding events are adjudicated per the BARC bleeding criteria shown in Table 2.

**Table 2 tbl2:** BARC bleeding criteria.

**Type 0:** No bleeding
**Type 1:** Bleeding that is not actionable and does not cause the patient to seek unscheduled performance of studies, hospitalization, or treatment by a healthcare professional; may include episodes leading to self-discontinuation of medical therapy by the patient without consulting a healthcare professional
**Type 2:** Any overt, actionable sign of hemorrhage (eg, more bleeding than would be expected for a clinical circumstance, including bleeding found by imaging alone) that does not fit the criteria for type 3, 4, or 5 but does meet at least 1 of the following criteria: (1) requiring nonsurgical, medical intervention by a healthcare professional, (2) leading to hospitalization or increased level of care, or (3) prompting evaluation
**Type 3a:** Overt bleeding plus hemoglobin drop of 3 to 5 g/dL^a^ (provided hemoglobin drop is related to bleed); any transfusion with overt bleeding
**Type 3b:** Overt bleeding plus hemoglobin drop 5 g/dL^a^ (provided hemoglobin drop is related to bleed); cardiac tamponade; bleeding requiring surgical intervention for control (excluding dental/nasal/skin/hemorrhoid); bleeding requiring intravenous vasoactive agents;
**Type 3c:** Intracranial hemorrhage (does not include microbleeds or hemorrhagic transformation, does include intraspinal); subcategories confirmed by autopsy or imaging or lumbar puncture; intraocular bleed compromising vision
**Type 4:** CABG-related bleeding; perioperative intracranial bleeding within 48 h; reoperation after closure of sternotomy for the purpose of controlling bleeding; transfusion of 5 U whole blood or packed red blood cells within a 48-h period^b^; chest tube output 2L within a 24-h period
**Type 5a:** Probable fatal bleeding; no autopsy or imaging confirmation but clinically suspicious
**Type 5b**: Definite fatal bleeding; overt bleeding or autopsy or imaging confirmation

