### Analysis of primary efficacy end points

The incidence of access-related BARC type III or V bleeding events will be defined dichotomously as bleed or no bleed. The frequency and proportion of subjects with a primary efficacy end point will be calculated along with the upper 95% confidence bound. Success will be based on showing the confidence bound is less than the historical rate of 12.5%

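### The success rule tests an access-site-only bleeding rate against a 12.5% historical rate that counts all BARC III or V bleeding, so a device with no effect can be declared to reduce bleeding

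*Protocol article*

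**What the plan says.** The Primary end points section restricts the endpoint to the access site: "The primary end point is incidence of access-site related bleeding" of BARC type III or V. All BARC III or V bleeding, wherever it arises, is listed apart under Secondary end points and is only described. Non-access-site bleeding is a separate item under Safety end points.

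Under Sample size calculations and assumptions, the primary aim is to show that the "incidence rate of access site-related BARC type III or V bleeding is reduced compared with the historical incidence rate". The only historical rate given comes from a cited study of 216 patients having Impella-supported high-risk PCI: "Investigators reported a major bleeding rate (defined as BARC III or V bleeding) of 12.5" percent. The planned effect follows: "a 50% reduction in access-site bleeding rate (P) under surveillance with the EBBMS is estimated". The alternative is set at 6.25%: "Assuming that the rate of bleeding (P) is 6.25%, a sample size of 184 evaluable subjects is required to achieve 90% power", by a one-sample exact binomial test at one-sided 0.05. The choice of a 50% reduction is said to be one that "took into account that not all bleeding events are access-related".

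Under Analysis of primary efficacy end points, the threshold is fixed: "Success will be based on showing the confidence bound is less than the historical rate of 12.5" percent.

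**The concern.** The quantity tested and the value it is tested against count different events. As described, the 12.5% covers every BARC III or V bleed. The trial's numerator leaves out bleeds away from the access site. The plan itself treats the two as different, because it makes one the primary and the other a secondary endpoint.

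The effect size has the same fault. Half of 12.5% is 6.25%, and calling that a halving of access-site bleeding is right only if every historical bleed was at the access site. The same paragraph says that this is not so.

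At stake is the trial's only success criterion. Leaving non-access bleeds out of the count lowers the expected rate below 12.5% before the device does anything. The nominal 5% error then does not apply to the stated aim, and a positive result could not be read as less access-site bleeding.

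**Working it through.** **Inputs from the protocol article.** Null rate p0 = 0.125; alternative p1 = 0.0625; n = 184 evaluable; exact one-sample binomial test, one-sided alpha 0.05; success if the upper 95% bound lies below 12.5%.

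**Input not in the document.** The share s of the historical 12.5% that was access-site related. It is assumed here, from 100% down to 50%.

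**Step 1: reproduce the stated design.** The critical count c is the largest k with P(X ≤ k | 184, 0.125) ≤ 0.05.
- P(X ≤ 15) = 0.0416 and P(X ≤ 16) = 0.0686, so c = 15.
- As confidence bounds: 15/184 = 8.15% has a one-sided exact upper 95% bound of 12.28%, which passes. 16/184 = 8.70% has a bound of 12.91%, which fails.
- Power: P(X ≤ 15 | 184, 0.0625) = 0.885, against 90% stated. The normal approximation gives N = 187.

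The design reproduces closely enough. The arithmetic is not the problem.

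**Step 2: chance of success with no device effect.** With no effect, the true access-site rate is 12.5% × s, and the chance of success is P(X ≤ 15 | 184, 0.125 × s).

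**Step 3: power against a like-for-like null.** Set the null to 12.5% × s, find the new critical count at n = 184, and compute power for a true halving to 6.25% × s. The last column is the smallest N whose exact power reaches 90%.

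| Share s (assumed) | Access-site rate, no effect | P(success), no effect, rule as written | Matched-null critical count | Power for a true halving, n = 184 | Smallest N for 90% |
|---|---|---|---|---|---|
| 100% | 12.5% | 4.2% | 15 | 88.5% | 191 |
| 95% | 11.875% | 6.9% | – | – | – |
| 90% | 11.25% | 10.9% | 13 | 84.4% | 212 |
| 80% | 10.0% | 24.3% | 11 | 78.8% | 239 |
| 75% | 9.375% | 33.9% | 10 | 75.3% | 255 |
| 70% | 8.75% | 45.2% | 9 | 71.3% | 274 |
| 60% | 7.5% | 69.4% | 7 | 61.4% | 320 |
| 50% | 6.25% | 88.5% | 5 | 48.5% | 385 |

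At a 50% share the no-effect rate equals the planned alternative, so an inert device succeeds as often as the planned effective one.

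**Step 4: what 6.25% means for the device.** If the share is s, reaching 6.25% needs an access-site reduction of 1 − 6.25/(12.5 × s) = 1 − 0.5/s. That is 44.4% at s = 90%, 37.5% at 80%, 28.6% at 70% and 0% at 50%. It equals the stated 50% only at s = 100%.

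**Step 5: power if the 12.5% rule is applied to all BARC III or V bleeding.** Suppose the device halves access-site bleeds and leaves the others alone. The all-bleeding rate is then 12.5% × (1 − s/2), and the critical count stays at 15.

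| Share s (assumed) | All-bleeding rate | Power, n = 184 |
|---|---|---|
| 90% | 6.875% | 80% |
| 80% | 7.5% | 69% |
| 70% | 8.125% | 57% |
| 50% | 9.375% | 34% |

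**The case against.** The strongest reply is that the historical source is not at hand. The article gives the 12.5% in one condensed sentence, and the next sentence handles it as an access-site baseline. The label may be loose and the number right, and the full protocol may justify it. This stands as a limit: what is shown is a mismatch in the stated definitions, not a known numerical error in the benchmark. As written, though, the 12.5% has no site restriction, and nothing in the article says otherwise.

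Second, the inflation depends on an assumed share. It runs from none at 100%, through 6.9% at 95%, to severe at 50%, and the article gives no support for any one value. That is fair. Only the direction is certain, although the 5% level is already exceeded at a 95% share.

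Third, the sponsor did consider that some bleeding is not access-related. But that remark supports the size of the reduction, which is the alternative. It leaves the null at 12.5%. If the 50% was meant to absorb the narrower endpoint, then part of the planned reduction consists of bleeds that are no longer counted.

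Fourth, a single-arm comparison with a fixed historical rate cannot isolate a device effect even when the definitions match. That is true, and the Limitations section names the single-arm design. It does not mention that the endpoint and benchmark count different events, and this part is avoidable.

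**Conclusion.** The concern holds. The null value in the success rule is, by the article's own description, the rate of a broader event than the primary endpoint counts. The stated one-sided 5% error does not hold for the aim of showing reduced access-site bleeding unless all the historical bleeds were at the access site. If 90% were, the no-effect chance of success is about 11%; if 80%, about 24%; if 70%, about 45%. Those sizes rest on the assumed share, on the exact binomial rule of 15 or fewer events in 184, and on a trial population whose underlying bleeding risk equals the historical one. The conclusion would fall away only if the 12.5% were itself an access-site rate. Because the sole success criterion is affected, this must be settled before a positive result is interpreted.

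**What to change.** Compare like with like, in both Sample size calculations and assumptions and Analysis of primary efficacy end points.

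- **Preferred:** replace 12.5% with the access-site-related BARC III or V rate from the same historical study, or from another source using that definition. Restate the alternative, the critical count and the power. If the 12.5% is already an access-site rate, say so and cite the definition.
- **If the source cannot be split by site:** apply the 12.5% rule to all BARC III or V bleeding, which is already a secondary endpoint. Report the access-site rate with its confidence bound and make no claim of reduction against 12.5%.
- **Another possible source:** the chart review of about 150 Impella cases without the monitor, planned under Health economics, if its bleeds are classified by the same access-site definition. A rate from about 150 patients has its own sampling error, which the analysis would have to carry.

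The cost is wording plus a less favourable power statement. At 184 subjects, a matched access-site null gives 84.4% power at a 90% share, falling to 48.5% at a 50% share. The all-bleeding test gives about 80% falling to 34% over the same range. No new patients are needed if that power is accepted. Restoring 90% against a matched access-site null would take at least 212 subjects at a 90% share, 239 at 80% and 385 at 50%.

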## Design of the SAFE-MCS study

The Safe Surveillance of PCI Under Mechanical Circulatory Support with the Saranas Early Bird Bleed Monitoring System (SAFE-MCS; NCT05077657) is a multicenter, single-arm, open-label study to evaluate the safety of complex high-risk PCI using the Impella (Abiomed) in conjunction with the Saranas EBBMS. The study will enroll 184 evaluable subjects at up to 15 US centers. Evaluable subjects are defined as all participants who had an EBBMS placed ipsilateral to MCS and had postprocedural monitoring by the EBBMS for a minimum of 2 hours. The study is anticipated to be approximately 24 months in duration. The duration of each subject’s participation will be the duration of the index hospitalization. The study is funded by Saranas, Inc, with an independent clinical events adjudication committee (Cardiovascular Research Foundation) and an independent imaging core laboratory (Medical Metrics).

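### At 184 subjects the named exact binomial test has 88.5% power, not the stated 90%: a small misstatement that needs only rewording

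*Protocol article*

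**What the plan says.** Two places in the protocol article bear on this.

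- **Sample size calculations and assumptions.** The historical comparator is taken from an earlier Impella trial: "Investigators reported a major bleeding rate (defined as BARC III or V bleeding) of 12.5" per cent. The design then supposes that "a 50% reduction in access-site bleeding rate (P) under surveillance with the EBBMS is estimated", which gives the planning rate: "Assuming that the rate of bleeding (P) is 6.25" per cent. From these it concludes that "a sample size of 184 evaluable subjects is required to achieve 90% power for a 1-sample exact binomial test". The level is fixed in the same sentence: "1-sample exact binomial test at the 1-sided 0.05 alpha level".
- **Analysis of primary efficacy end points.** The proportion with the event "will be calculated along with the upper 95% confidence bound". The success rule follows: "Success will be based on showing the confidence bound is less than the historical rate of 12.5" per cent.

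The 184 are evaluable subjects (Design of the SAFE-MCS study: "The study will enroll 184 evaluable subjects at up to 15 US centers"), so the power calculation needs no further allowance for attrition.

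**The concern.** The power statement is fully specified: null rate, alternative rate, number of subjects, test, level and sidedness are all given. It can therefore be checked directly, and the exact test at 184 does not return 90%. An exact calculation already allows for the discreteness of the binomial distribution, so a figure labelled as exact should be the attained one.

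What is at stake is modest. The power for the primary end point is a figure that readers and the sponsor rely on. The chance of missing a true halving of the bleeding rate is 11.5% (100% − 88.5%), not the 10% implied. The article also does not state the number of events at which the study succeeds, and giving it would make the design plain.

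**Working it through.** **Inputs** (all from the protocol article)

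- Null rate p0 = 0.125: success rule, and the historical rate in the sample size section
- Alternative rate p1 = 0.0625: sample size section, half of 0.125
- n = 184 evaluable; one-sample exact binomial test; one-sided alpha 0.05: sample size section

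**Step 1. Critical value.** Find the largest c with P(X ≤ c | 184, 0.125) ≤ 0.05.

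| c (events) | c/184 | P(X ≤ c) at 12.5% | P(X ≤ c) at 6.25% |
|---|---|---|---|
| 14 | 7.61% | 0.0236 | 0.8220 |
| 15 | 8.15% | 0.0416 | 0.8854 |
| 16 | 8.70% | 0.0686 | 0.9301 |

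Fifteen is the largest count that keeps the error at or below 0.05, so the test succeeds at 15 or fewer events with attained alpha 0.0416.

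**Step 2. Power.** P(X ≤ 15 | 184, 0.0625) = 0.8854. The stated figure is 0.90, so the shortfall is 0.90 − 0.885 = 0.015, or 1.5 points.

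**Step 3. Where the exact test reaches 90%.** Repeating steps 1 and 2 for each n from 10 upwards, no n below 191 gives 90%. Selected values:

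| n | pass mark | attained alpha | power |
|---|---|---|---|
| 181 | ≤ 15 | 0.0490 | 0.8969 |
| 184 | ≤ 15 | 0.0416 | 0.8854 |
| 190 | ≤ 15 | 0.0296 | 0.8605 |
| 191 | ≤ 16 | 0.0478 | 0.9090 |
| 194 | ≤ 16 | 0.0407 | 0.8989 |
| 200 | ≤ 17 | 0.0490 | 0.9226 |

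The curve is a sawtooth. Power falls as n grows until the pass mark moves up by one event. After 191 it dips just below 90% again at 194–199 and 208–209.

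**Step 4. Could an approximation give 184?** With null and alternative variances,

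n = [(1.6449·√(0.125·0.875) + 1.2816·√(0.0625·0.9375)) / 0.0625]² = [(0.5440 + 0.3102) / 0.0625]² ≈ 186.8, so 187.

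At n = 184 the same approximation gives Φ[(0.0625·√184 − 0.5440) / 0.2421] = Φ(1.255) = 0.895. The arcsine formula gives 181.2, so 182. Both lie close to 184, but neither returns it exactly and neither is the named test.

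**Step 5. Does the success rule agree with the test?** The one-sided 95% Clopper-Pearson upper bound is 12.28% at 15 of 184 (below 12.5%, success) and 12.91% at 16 of 184 (above, failure). It gives the same pass mark as the exact test in step 1.

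**The case against.** The strongest reply is that this is rounding-level imprecision. The gap is 1.5 points, and a check allowing two points either way would accept the figure. The normal approximation gives 89.5% at 184. The shortfall comes from the discreteness of the test, which spends 4.16% rather than 5%, and power on a sawtooth depends heavily on where n happens to fall. No decision changes. All of this stands as an argument about severity. It does not make the sentence correct, because the article names the exact test and says that 184 is the number needed for 90% with it.

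A reader might also infer something stronger from the success rule: because the type of bound is not named, the pass mark could be 14, 15 or 16 events, the rule could displace the exact test, or the 0.05 level could be broken. The documents do not support this.

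- A single upper 95% bound is the ordinary counterpart of a one-sided 0.05 test. Read with the sample size section, it gives 15.
- A mark of 14 needs the upper limit of a two-sided 95% exact interval (12.44% at 14, 13.09% at 15; power 82.2%). That is in effect a 0.025 test and contradicts the stated one-sided 0.05.
- A mark of 16 needs a one-sided Wald bound (12.11% at 16; true error 6.9%). The article does not mention this method, and it is not exact. One-sided Wilson (12.74%) and Jeffreys (12.59%) bounds both fail at 16, as Clopper-Pearson does.
- Comparing a one-sided exact bound with 12.5% is the exact test in another form, so nothing is replaced.

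The interval formula is also a detail commonly left to the full protocol or the analysis plan, neither of which is shown. Its absence from an article is not a defect.

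**Conclusion.** The stated power is slightly too high for the test that the article names: 88.5% at 184 evaluable subjects against 90% claimed, with 15 or fewer events as the pass mark and an attained one-sided error of 4.2%. Strictly, 191 is the first sample size at which the exact test has 90% power. Severity is low. The sample size is not invalidated, the type I error is held below 0.05, and the success rule is consistent with the test.

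The conclusion assumes exactly 184 evaluable subjects and takes both 12.5% and 6.25% as the article states them. A different evaluable number would shift both the pass mark and the power along the sawtooth in step 3.

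**What to change.** Restate the sentence under Sample size calculations and assumptions along these lines: *With 184 evaluable subjects, the exact one-sided 0.05 test succeeds if 15 or fewer subjects (8.15%) have the event; the attained alpha is 4.2% and the power is 88.5% at a true rate of 6.25%.*

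Optionally, under Analysis of primary efficacy end points, name the bound as the one-sided 95% exact (Clopper-Pearson) upper bound. This matches the sizing test and leaves the decision unchanged.

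The cost is wording only. No patients are added, and the one drawback is a slightly less favourable stated power.

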### Analysis of primary efficacy end points

The incidence of access-related BARC type III or V bleeding events will be defined dichotomously as bleed or no bleed. The frequency and proportion of subjects with a primary efficacy end point will be calculated along with the upper 95% confidence bound. Success will be based on showing the confidence bound is less than the historical rate of 12.5%

### Analysis of secondary efficacy end points

The frequency and percentage of activation of each EBBMS indicator (none/level 1/level 2/level 3) and all BARC type III or V bleeding (no bleeding/type III/type V) will be assessed.

### Assessment of safety

Safety will be assessed from device- and procedure-related adverse events, serious adverse events, and serious adverse device effects. The rate of each type of safety outcome as well as overall safety events will be computed for the study population. Safety and tolerability will be assessed by evaluating reported adverse events as well as any postprocedural changes in values from baseline of clinical laboratory assessments. The incidence of treatment-emergent adverse events will be reported overall and by severity and relatedness to study intervention. Adverse events causing study discontinuation and serious adverse events will be listed and tabulated.

### Limitations

Although the SAFE-MCS study is the first study dedicated to evaluate bleeding events post-Impella use, some limitations exist. First, the current study is a single-arm study, with no randomization to patients undergoing high-risk PCI with Impella support with no Saranas EBBMS. Second, the sample size is modest. Third, patients in cardiogenic shock or ST-elevation myocardial infarction were excluded. Those patients are known to have high bleeding risk and could have enriched our study population. Future studies will target specifically those patients.
